### Study Design and Setting

3.1

This is a randomised trial conducted at the surgical Prehabilitation Program at the University Health Network (UHN), a large tertiary academic hospital network in Toronto, ON. Participants will be randomised 1:1 to intervention (PSP+PREHAB): active comparator (PREHAB). Flow of participants is depicted in Figure 1. The initial study protocol has been approved by the University Health Network Research Ethics Board. The trial is registered with ClinicalTrials.gov (ID NCT06762639). This protocol was reported in adherence with the Standard Protocol Items: Recommendations for Interventional Trials (SPIRIT) checklist (SPIRIT 2013 Checklist: Recommended Items to Address in a Clinical Trial Protocol and Related Documents n.d.). The checklist is available in the Supporting Information (Appendix S2).

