### Randomisation and Blinding

3.5

Participants will be randomised 1:1 (PSP+PREHAB: PREHAB) using a computer‐generated randomisation sequence. This randomisation process will be blinded such that the research team member who generates the randomisation sequence is not in contact with interventionists, outcome assessors or the participant's circle of care. Due to the nature of the study, participant and interventionist (PSP) blinding is not possible. However, outcome assessors and clinicians delivering PREHAB will be blinded to group allocation.

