Demographic, physical fitness and anthropometric, clinical and patient‐reported outcomes are described in Appendix S7. Briefly, demographic characteristics will be documented via a standardised questionnaire. Physical fitness and anthropometric outcomes include the Six‐minute Walk Test (6MWT), short physical performance battery, timed up and go, grip strength, body mass index (BMI) and body composition via bioelectrical impedance analysis (mBCA 514, Seca, Hamburg, Germany). Clinical outcomes include hospital length of stay, readmission and surgical complications documented via patient medical record up to 90 days after surgery. Patient‐reported outcomes include the Edmonton Frail Scale (Rolfson et al. 2006) and Canadian Nutrition Screening Tool (CNST) (Laporte et al. 2015) administered at baseline and the PROMIS‐29+2 profile (Fries et al. 2009) administered at all timepoints.

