### Analytic Plan

4.1

All data will be collected and imported into R version 4.1.2 for statistical analysis; an alpha of 0.05 will be used. Participant characteristics will be summarised using means (SD) or medians [IQR] for continuous variables and frequency (%) for categorical variables. We will report reasons for exclusion and attrition, as well as safety or adverse events with frequency and percentages.

The statistical analysis plan was created in consultation with a UHN biostatistician. The primary outcome (PSQI score) will be compared between the two treatment arms using analysis of covariance (ANCOVA), controlling for baseline PSQI score. A linear mixed effects model will be used to compare treatment arms with respect to the longitudinal PSQI scores (baseline, preoperative, 6 weeks post‐surgery). Point estimates and 95% confidence intervals will be calculated for changes in the PSQI between groups at each timepoint. We will use Q–Q plots and histograms to assess data normality. If non‐normality is encountered and cannot be corrected through data transformations (e.g., log, square root), we will employ appropriate non‐parametric alternatives, such as the Mann–Whitney U test for between‐group comparison. Model assumptions including homogeneity of variance (Levene's Test) and normality of dependent variables (Shapiro–Wilk Test) will be used. Independence of observations was assessed using the Durbin Watson (DW) statistic, with values between 1.5 and 2.5 indicating independence. Sensitivity analyses will address potential loss to follow‐up by replacing the missing outcome measurements with best or worst values to assess the robustness of our results. In the unlikely event of unbalanced baseline characteristics between the treatment arms, the mixed effects models will be adjusted for these potential confounders (e.g., age, sex, etc.). Conclusions will be drawn using comparisons of each time point between groups. The minimum clinically important difference for the PSQI score will be 1.3 based on previous research (Shergis et al. 2016). Given a lack of consensus for the PSQI MCID, previous research has interpreted any statistically significant change in the PSQI to be clinically meaningful (Shergis et al. 2016).

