Additional exploratory analyses using linear mixed effect models will be conducted to understand the effect of the intervention on secondary outcomes that are measured longitudinally, including physical fitness (e.g., 6MWT) outcomes and the PROMIS‐29+2. For outcomes that are measured at only one time point (e.g., length of hospital stay), we will use non‐parametric Wilcoxon signed‐rank *t*‐tests or Chi‐square tests for continuous and categorical outcomes, respectively. Given the exploratory nature of secondary outcomes, *p*‐values will be adjusted using Bonferroni corrections to account for multiple comparisons. All analyses will be conducted using the intention to treat principle. The data will be reported in accordance with the Consolidated Standards of Reporting Trials (CONSORT) guidelines for reporting randomised trials (Schulz et al. 2010).

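### The signed-rank test named for continuous outcomes measured once does not fit a comparison of two independent arms; it is probably a naming slip for the rank-sum test

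*Protocol article*

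**What the plan says.** The last part of the Analytic Plan (section 4.1) deals with secondary outcomes. Its stated aim is "to understand the effect of the intervention on secondary outcomes". Longitudinal outcomes go to linear mixed models. The rest are introduced by "For outcomes that are measured at only one time point (e.g., length of hospital stay", and for the continuous ones the plan states "we will use non‐parametric Wilcoxon signed‐rank", followed by the word t-tests; categorical ones get chi-square tests. The paragraph calls these outcomes exploratory ("Given the exploratory nature of secondary outcomes") and applies a Bonferroni correction.

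The design is given in two places. Study Design and Setting (3.1) says "Participants will be randomised 1:1 to intervention (PSP+PREHAB): active comparator (PREHAB". Randomisation and Blinding (3.5) says that allocation is made "using a computer‐generated randomisation sequence". Neither section mentions matching or pairing.

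Earlier in section 4.1, in the paragraph on the primary outcome, the fallback for non-normal data is a non-parametric method "such as the Mann–Whitney U test for between‐group comparison".

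**The concern.** The named test and the design do not go together. A signed-rank test ranks the absolute values of differences within pairs, or of deviations from a fixed value in one sample. An outcome recorded once per patient gives no within-patient difference, and an unmatched two-arm trial gives no natural pair across arms. The added word t-tests makes the phrase describe no actual procedure.

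This is not a detail left to a fuller analysis plan: the article names a test, and the test is the wrong one for the comparison. At stake is the analysis of length of stay, a listed clinical outcome that the Introduction uses to motivate the trial. If the wording stands, the team must either apply a test that does not fit or depart from its published plan at analysis.

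**Working it through.** The plan gives no figure that depends on this choice, so there is none to reproduce. The argument rests on the text; the simulations only show how much it matters.

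**1. What the comparison is.** The aim is the effect of the intervention, so it is arm against arm. The arms are independent (1:1 allocation, no matching). Each patient has one value.

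**2. What the named test needs.** Either differences D_i = X_i − Y_i from real pairs, or one sample tested against a fixed location. The design supplies no real pairs, and a one-sample test does not compare arms.

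**3. Which outcomes are reached.** Section 4 states: "Clinical outcomes include hospital length of stay, readmission and surgical complications documented via patient medical record up to 90 days after surgery". Of these, length of stay is the evidently continuous one. Readmission and complications would fall under chi-square if analysed as categorical.

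**4. What happens if it is run as written.** The documents give no distribution for length of stay. Assumed here: lognormal stays with log-SD 0.7, log-mean 1.5 in the reference arm, and two-sided alpha 0.05 (the plan gives 0.05 without sidedness). The 64 per arm is the evaluable number in section 3.3.

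- *Unequal arms (65 and 63):* the paired test cannot be computed.
- *Equal arms (64 and 64), one dataset, log-means 1.5 and 1.2:* the rank-sum p-value is fixed at 0.00098. Over 2,000 arbitrary pairings of the same values, the signed-rank p-value ran from 0.00004 to 0.029. All 2,000 were below 0.05. The planned Bonferroni threshold is 0.05/m for m comparisons. The article does not give m, but already at m = 2 the threshold is 0.05/2 = 0.025, which lies inside that range. Row order alone could then decide the result, at least at the extremes.
- *One-sample test within an arm:* p is about 4 × 10⁻¹², simply because stays are positive.

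**5. Does arbitrary pairing bias the test?** If the arms have the same distribution and row order is unrelated to outcome, X − Y is symmetric about zero, so the signed-rank test keeps its level. In 4,000 simulated trials of 64 per arm:

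| | Signed-rank, arbitrary pairs | Rank-sum |
|---|---|---|
| Type I error | 0.047 | 0.047 |
| Power, assumed log-scale shift 0.35 | 0.74 | 0.78 |

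The Monte Carlo standard error at 0.05 is √(0.05 × 0.95 / 4,000) = 0.003, so both error rates agree with the nominal level. The power loss is about 0.78 − 0.74 = 0.04.

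**6. Does another part of the document correct it?** The Mann–Whitney U test is the two-sample test that this comparison needs, but it appears only as the PSQI fallback. It does not govern the sentence on single-time-point outcomes.

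**The case against.** The strongest reply is that this is a slip of the pen. The phrase as printed describes no real test, and the same section names the correct two-sample rank test for a between-group comparison, so the authors evidently know it and would probably run it. The outcomes are secondary and exploratory, and the correction is one of wording. All of this stands, and it is why the point should not be rated as a serious flaw.

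Two stronger readings are tempting, and the documents do not support either. A reader might infer that no way of running the named test says anything about the treatment effect, or that false positives would be inflated. That is true neither of equal arms nor of arbitrary pairing: there the test still addresses the difference between arms, holds its level and loses a little power. The fault in that case is a p-value that cannot be reproduced without the row order. A reader might also infer that the authors intend a paired or matched analysis, or that the trial's main result is at risk. No matching is described anywhere, and the primary PSQI comparison is an ANCOVA.

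The reply does not remove the point. A probable slip in a published analysis rule is still the rule until it is corrected, and nothing else in the document corrects it.

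**Conclusion.** The point holds in limited form. The named test does not apply to continuous outcomes measured once in two independent, unmatched arms. Taken literally, it is either not computable, dependent on arbitrary ordering, or a test of a different hypothesis. That conclusion follows from the text alone and needs no assumed figure.

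The severity is moderate to minor. The reach is single-time-point continuous secondary outcomes, chiefly length of stay. The primary ANCOVA, the longitudinal mixed models and the sample size are untouched. The simulated p-values, error rates and power are illustrative: they depend on assumed lognormal stays and shifts, and the p-value range belongs to one simulated dataset.

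**What to change.** In the Analytic Plan (4.1), replace the signed-rank wording, including the word t-tests, with Wilcoxon rank-sum (Mann–Whitney U) tests for continuous outcomes measured once. This agrees with the between-group test already named for the PSQI fallback, and it is defined for any arm sizes. The cost is a few words, best changed before any outcome data are analysed; no recalculation or design change follows. Reporting a Hodges–Lehmann difference with a 95% confidence interval for length of stay would be a useful option, but it is not needed to correct the error.

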## Objectives

2

The primary objective of this study is to evaluate the effectiveness of a personalised sleep prehabilitation (PSP) intervention in addition to standard‐of‐care multimodal prehabilitation (PREHAB) on participant sleep health versus standard‐of‐care multimodal prehabilitation alone (i.e., PSP+PREHAB vs. PREHAB). Secondary objectives include examining the impact of the intervention on anthropometric, physical fitness, patient‐reported, clinical and other sleep health outcomes. A full list of study research questions is available in Appendix S1.

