### Sample Size

3.3

A total of 154 participants will be recruited for this study. The sample size was computed by a biostatistician at UHN for an ANCOVA design in which the Pittsburgh Sleep Quality Index (PSQI) score will be compared between the two arms at the preoperative timepoint, controlling for baseline scores. Assuming a PSQI score mean of 11.9 (SD 2.6) points for the usual care arm (Atoui et al. 2023) with no correlation between baseline and preoperative scores, a sample size of 64 participants per arm (128 total) will be required to detect a difference in mean PSQI score of 1.3 points, which is the minimum clinically important difference (Longo et al. 2021). This difference between the two arms corresponds to a Cohen's d effect size of 0.5 with 80% power and an alpha of 0.05. The final sample accounts for 20% attrition.

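### Minor, cheap improvement: Holm's step-down method would give the secondary outcomes the same 5% family-wise error control as the planned Bonferroni correction and never reject fewer of them

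*Protocol article*

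**What the plan says.** The Analytic Plan (4.1) sets a general level: "an alpha of 0.05 will be used". The primary PSQI comparison is a separate ANCOVA. For the rest, the plan reasons: "Given the exploratory nature of secondary outcomes", the p-values "will be adjusted using Bonferroni corrections to account for multiple comparisons". It names no step-down variant, and the unqualified term ordinarily means the single-step method, in which each p-value is compared with 0.05/m for a family of m tests.

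The article does not give m. The Objectives section lists domains only: "Secondary objectives include examining the impact of the intervention on anthropometric, physical fitness", followed by patient-reported, clinical and other sleep outcomes. Study Outcomes (4) names walking distance, physical performance, grip strength, body composition, PROMIS-29+2, sleep diary, sleep self-efficacy, length of stay, readmission and complications, among others. A family of 10 to 20 tests is therefore plausible, but it is an assumption.

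**The concern.** The plan has already decided to adjust the secondary outcomes, so the remaining question is which adjustment to use. Bonferroni holds every outcome to the strictest threshold, 0.05/m, however many others have already been rejected. Holm relaxes the threshold after each rejection and needs no further assumption to do so.

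At stake is power in a part of the trial that has little to spare. The sample size was set for the PSQI alone, with an "effect size of 0.5 with 80% power and an alpha of 0.05". An outcome tested at 0.05/m falls well below 80% power at that effect size. Any power that can be recovered without loosening the error bound is worth having, even if it is little.

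**Working it through.** **Inputs from the article (Sample Size, 3.3).** The trial is sized "to detect a difference in mean PSQI score of 1.3 points". The SD comes from "Assuming a PSQI score mean of 11.9 (SD 2.6) points for the usual care arm", and the calculation is made "with no correlation between baseline and preoperative scores". Hence d = 1.3/2.6 = 0.5. The article gives 64 evaluable per arm, 154 recruited and 20% attrition.

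**The plan's own figure.** n per arm = 2(z₀.₉₇₅ + z₀.₈₀)²/d² = 2(1.960 + 0.842)²/0.25 = 62.8, or 63. The t-test version gives 63.77, or 64. The stated 64 reproduces with a two-sided test.

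**Why Holm cannot reject fewer.** Order the p-values from smallest to largest. Holm compares them in turn with 0.05/m, 0.05/(m−1), …, 0.05 and stops at the first failure. No threshold is below 0.05/m, so every p-value that passes Bonferroni also passes Holm. Example with m = 20 and smallest p-values 0.0010 and 0.0026: Bonferroni's threshold is 0.05/20 = 0.0025, so it rejects only the first. Holm's second threshold is 0.05/19 = 0.00263, so it rejects both.

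**Power under Bonferroni.** Take 62 per arm (154 × 0.80 = 123.2, halved to 61.6). For d = 0.5 the test statistic is centred at 0.5 × √(62/2) = 2.784.
- m = 20: critical value 3.023 (two-sided 0.0025); power Φ(2.784 − 3.023) = about 40%.
- m = 15: critical value 2.935; power Φ(−0.151) = about 44%.
- m = 20 at d = 0.3: centre 1.670; power Φ(1.670 − 3.023) = about 8.8%.

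**Holm against Bonferroni by simulation.** Equicorrelated normal test statistics, 62 per arm, correlation 0.3. The family size, the number of affected outcomes and d are all assumptions. Power is the average per truly affected outcome.

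| Affected / family | d | Bonferroni | Holm | Gain (points) |
|---|---|---|---|---|
| 4 / 20 | 0.5 | 40.3% | 41.1% | 0.8 |
| 2 / 10 | 0.5 | 49.1% | 49.9% | 0.8 |
| 10 / 20 | 0.5 | 40.4% | 43.3% | 2.9 |
| 15 / 20 | 0.5 | 40.9% | 46.1% | 5.2 |
| 15 / 15 | 0.5 | 44.2% | 54.7% | 10.5 |
| 10 / 20 | 0.3 | 8.8% | 9.2% | 0.4 |
| 15 / 15 | 0.3 | 10.2% | 11.7% | 1.5 |

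Repeat runs moved the levels by a few tenths of a point (4 of 20 also came out at 40.6% and 41.5%). At d = 0.2 the gain was at most 0.2 points in every case tried.

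**Second set of assumptions.** With 64 per arm, d = 0.5, families of 5, 10, 15 and 20, correlation 0 or 0.5 and 100,000 replicates per scenario:
- No outcome in any replicate was rejected by Bonferroni and not by Holm.
- The family-wise error of both methods was at most 0.050. Holm uses more of that allowance: with 10 of 20 affected and correlation 0.5 it was 0.020 under Bonferroni and 0.029 under Holm.
- The gain ran from about 0.04 points (1 of 5 affected, correlation 0.5) to about 11.5 points (all of 5 or all of 10 affected, correlation 0).

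**The case against.** The strongest case for leaving the plan alone has four parts.

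- **Bonferroni is valid, conservative and pre-specified, and the outcomes are called exploratory.** This stands. No confirmatory claim depends on the choice, and the point is one of efficiency, not of type I error.
- **The size of the gain cannot be read from the article.** This stands too. The family may be defined, or split by domain, in an appendix or analysis plan that is not shown. That would change the size of the gain but not its direction.
- **The large gains need unlikely scenarios.** A reader might infer from the 44% to 55% row that the plan is set to miss many real effects. The documents do not support that. The value d = 0.5 is the planning difference for the PSQI. Nothing in the article suggests that a sleep intervention, added to prehabilitation that both arms receive, shifts grip strength, body composition and readmission alike by half an SD. Low power here comes mainly from testing many outcomes at this sample size, and Holm does not cure that.
- **Bonferroni has uses of its own.** A reader might call the planned choice a pure loss, and that also goes too far. Bonferroni has simple matching simultaneous intervals, and each outcome can be judged without waiting for the others. Here outcomes mature before surgery, at 6 weeks and up to 90 days after surgery. The plan does not draw on these advantages, however: it promises 95% intervals only for the PSQI and describes no staged release of secondary results.

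**Conclusion.** The point holds as a minor improvement, not as an error. For the family the plan intends to adjust, Holm gives the same 5% family-wise bound under any dependence and never rejects fewer outcomes. That follows from the thresholds and needs no assumption about this trial.

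The size does rest on assumptions (62 per arm, correlation 0.3, and the family size, effect and share affected as tabulated). It is under 1 point of per-outcome power when few of the outcomes respond or when about half respond modestly, about 3 to 5 points with 10 to 15 of 20 affected at d = 0.5, and about 10 points only when every outcome responds at that size. The first range is the more plausible one for this intervention. The primary ANCOVA and the sample size do not change.

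**What to change.** In the Analytic Plan, state that the secondary p-values will be Holm-adjusted, in place of the Bonferroni correction, over the same family. Make the change before unblinding. Report 95% confidence intervals for the secondary outcomes alongside and label them as unadjusted.

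The cost is one word in the plan and one argument in R, which the plan already uses. Two consequences should be accepted openly. An unadjusted interval may exclude zero while the Holm-adjusted p-value is not significant, so the label matters. All p-values of a family must also be available before any can be adjusted, so a family that includes the 90-day clinical outcomes has to wait for them.

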## Discussion

5

As effectiveness, implementation and economic data supporting prehabilitation grows, continued advancements are warranted (Randall et al. 2024). This protocol describes a randomised trial aiming to expand the delivery of prehabilitation to include a novel intervention modality. Findings will inform the integration of sleep assessment, measurement and intervention in the preoperative setting.

The relationship between sleep health and overall health is well documented, and several studies have demonstrated the importance of sleep for surgical recovery. Capitalising on the preoperative window to address surgical risk factors has significantly improved patient care in recent decades (McIsaac et al. 2022). Within our clinically integrated prehabilitation service in Toronto, Canada, we have recognised the significant prevalence of sleep disruption as a limitation to functional capacity.

Although at least 47 interventions have been initiated preoperatively and measured a sleep outcome, (Sibley et al. 2024) to our knowledge, no study has evaluated the effectiveness of a sleep‐specific intervention preoperatively. Very few studies within the prehabilitation literature have acknowledged the importance of sleep. In 2023, Atoui and colleagues (2023) conducted a pilot RCT evaluating the effect of home‐based multimodal prehabilitation on sleep health versus usual care (Atoui et al. 2023). The intervention did not demonstrate improvements to within‐ or between‐group self‐reported (PSQI) or device‐measured sleep at any time point. As such, despite the well‐documented relationships between exercise, nutrition, and psychological stress (i.e., standard multimodal prehabilitation), these strategies may not sufficiently address disturbed preoperative sleep health (Kekecs et al. 2014; Knoerl et al. 2022). The PSP intervention was curated to be integrated into the prehabilitation workflow at our institution. The protocol also builds on other studies that have successfully integrated digital technology and behaviour change techniques into prehabilitation interventions (Blumenau Pedersen et al. 2023; Fong et al. 2023). The BBTI is the main component of the intervention. Not only is this an evidence‐based intervention with proven efficacy, but it was designed to be delivered by non‐experts (Gunn et al. 2019). As such, this intervention is generalisable to other prehabilitation settings.

Some strengths of this study include the randomised design with outcome assessors blinded to group allocation. The study will integrate and expand on a gold‐standard multimodal prehabilitation intervention including exercise, nutrition, psychological intervention and smoking cessation delivered by regulated health professionals with several years of experience delivering prehabilitation. The study will capture robust outcomes including demographic, physical and anthropometric, sleep health, clinical and patient‐reported outcomes. The analysis will be conducted using intention to treat. There are limitations to this study worthy of discussion. Selection bias will favour the surgical subgroups referred to the Prehabilitation Program during study recruitment as well as the physicians and patients who refer and accept referral to prehabilitation, respectively. The study will lack a true control group without intervention. This is warranted given the overwhelming evidence supporting prehabilitation. Given that the intervention is delivered by an interprofessional team of allied health professionals, the generalisability of this study to other lower‐resource settings can be considered a limitation. Finally, this study is being conducted without any formal published feasibility trials. As such, it is difficult to predict participant adherence to or satisfaction with the intervention. However, the sleep measures included within this protocol are being used in an ongoing prospective observational study of the same target population with acceptable rates of recruitment, satisfaction and data completeness.

